## Abstract

**Introduction:**

Smoking is a major avoidable cause of ill-health and premature death. Treatments that help patients successfully quit smoking have an important effect on health and life expectancy. Varenicline is a medication that can help smokers successfully quit smoking. However, there are concerns that it may cause adverse effects, such as increase in the occurrence of depression, self-harm and suicide and cardiovascular disease. In this study we aim to examine the effects of varenicline versus other smoking cessation pharmacotherapies on smoking cessation, health service use, all-cause and cause-specific mortality and physical and mental health conditions.

**Methods:**

In this project we will investigate the effects of varenicline compared to nicotine replacement therapies on: (1) long-term smoking cessation and whether these effects differ by area level deprivation; and (2) the following clinically-important outcomes: rate of general practice and hospital attendance; all-cause mortality and death due to diseases of the respiratory system and cardiovascular disease; and a primary care diagnosis of respiratory illness, myocardial infarction or depression and anxiety. The study is based on a cohort of patients prescribed these smoking cessation medications from the Clinical Practice Research Datalink (CPRD). We will use three methods to overcome confounding: multivariable adjusted Cox regression, propensity score matched Cox regression, and instrumental variable regression. The total expected sample size for analysis will be at least 180 000. Follow-up will end with the earliest of either an ‘event’ or censoring due to the end of registration or death.

**Ethics and dissemination:**

Ethics approval was not required for this study. This project has been approved by the CPRD's Independent Scientific Advisory Committee (ISAC). We will disseminate our findings via publications in international peer-reviewed journals and presentations at international conferences.

Strengths and limitations of this study
We will use data from a large sample of patients prescribed smoking cessation treatment in UK general practices. This means we will have substantial power to detect even relatively small effects, or effects on rare outcomes.We will use three statistical approaches to overcome confounding. These approaches depend on distinct assumptions. Triangulating across different methods will help provide more robust evidence about the effects of these medications.Our study will use observational data and so results can suffer from unobserved confounding. We will report in detail the confounding structure, and detail the methods we used to overcome this limitation.The outcomes used in this study will be defined using diagnoses and interactions that occur as part of the patients’ routine care. Different general practices may use a range of Read codes to record diagnoses. We will mitigate this limitation by using validated code lists, where available, to ensure the algorithms we use accurately capture the diagnoses and events of interest.

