### Power calculations

The following power calculations are based on effect sizes and CIs observed in our previously published results, which used data from 110 000 individuals prescribed either varenicline or nicotine replacement therapy.^13^ Based on the rate of 18 000 new prescriptions per year observed in the CPRD from 2006 to 2011,^13^ we estimate that with a further 4 years of follow-up the number of patients prescribed either varenicline or nicotine replacement therapy will have increased by 72 000. Therefore the total expected sample size for analysis will be around 180 000.

In our previous analysis using CPRD data the age-adjusted and sex-adjusted HR for self-harm/suicide for varenicline versus nicotine replacement therapy at 9 months was 0.73 (95% CI 0.54 to 0.99); after adjusting for possible confounders this became 0.90 (95% CI: 0.66 to 1.22).^13^ A 70% increase in sample size would lead to a reduction of the SE by a factor of 1.3, reducing the breadth of the above CI in the adjusted analysis from 0.56 to 0.43.

Rare outcomes, such as self-harm and suicide were used in previous analyses; in this project we will have greater power to explore more common outcome measures. For example, in the previous analysis the 9-month age-adjusted and sex-adjusted HR for all-cause mortality 9 months after first prescription for varenicline versus nicotine replacement therapy was 0.43 (95% CI 0.35 to 0.53); after controlling for possible confounders this became 0.49 (95% CI 0.40 to 0.61). A 70% increase in sample size would lead to a reduction of the SE by a factor of 1.3, reducing the breadth of the above CI in the adjusted analysis from 0.21 to 0.16.

For the effects of varenicline versus nicotine replacement therapy on all-cause mortality, instrumental variable analysis found a risk difference of 0.7 (95% CI −3.3 to 4.7) per 1000 patients treated after 9 months. We estimate that a 70% increase in sample size would narrow the CIs from 8.0 to 6.2.

Using data from our previous project, within 2 years of first prescription, we found 2517 admissions for respiratory disease among 1374 patients; 3144 admissions for cardiovascular disease among 1022 patients; and 3277 admissions for depression or anxiety among 213 patients. This is more events than we found for suicide and self-harm in our previous study; therefore we believe that there will be enough events for this analysis.

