To mimic an intention-to-treat analysis in an RCT, in our primary analysis patients who are initially prescribed nicotine replacement therapy, but later switch to varenicline, will be allocated to nicotine replacement therapy and vice-versa. We will use an intention-to-treat design for two reasons. First, while there are theoretical statistical models for estimating the effects of treatment switching such as marginal structural models, these methods require the strong assumption that there are no unmeasured confounders and typically require detailed data on time-varying confounders, which are unlikely to be available in the CPRD. Second, to our knowledge there are no instrumental variable methods to estimate the effects of switching treatment. However, we will investigate the number of participants who switch treatment as a sensitivity analysis.

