#### Analysis 1: Conventional cox regression

In our first analysis, a conventional observational analysis, we will estimate HRs of the outcomes using Cox-proportional hazards models and the actual prescriptions issued to the patients.^29^ Each patient's date of entry into the cohort will be the date they were first prescribed a smoking cessation therapy. The date of exit for each outcome will be the date on which they first have an event, or are censored due to end of follow-up or death or leaving the practice. We will report these associations adjusted for basic confounders (age and gender), and results adjusted for all measured covariates described above.

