#### Analysis 2: Propensity score regression

In our second analysis we will construct a sample of patients balanced on covariates and risk factors using a propensity score.^30–33^ We will construct propensity scores using a logistic regression of the actual treatment received on the covariates described above. Therefore, each participant's propensity score will be their conditional probability (odds) of receiving varenicline versus nicotine replacement therapy. We will match each patient receiving varenicline to another patient receiving nicotine replacement therapy with the closest propensity score on a ratio of 1:1 using a nearest neighbour algorithm with no replacement, and matching will be restricted to the common support region. Patients outside the common support region are those prescribed varenicline with propensity scores higher than any patient prescribed nicotine replacement therapy and vice-versa. We will estimate HRs of the outcomes using the propensity score matched sample using Cox regressions using the same entry and exit information as the conventional Cox regression analysis described above.

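### The Cox and propensity-matched analyses share the no-unmeasured-confounding assumption; on that threat only the instrumental variable analysis is distinct, and the article should say so

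*Protocol article*

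**What the plan says.** The strengths and limitations list, printed with the abstract, offers three statistical approaches to overcome confounding. It states "These approaches depend on distinct assumptions" and then "Triangulating across different methods will help provide more robust evidence about the effects of these medications". The next item concedes that "Our study will use observational data and so results can suffer from unobserved confounding", without saying which of the three methods are exposed.

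The Statistical analysis section defines the methods:

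- Analysis 1 is a Cox regression on the prescriptions actually issued, with "results adjusted for all measured covariates described above".
- Analysis 2: "We will construct propensity scores using a logistic regression of the actual treatment received on the covariates described above". Patients are matched 1:1 and "matching will be restricted to the common support region". A Cox regression with Analysis 1's entry and exit rules follows.
- Analysis 3 uses prescribing preference, proxied by seven prior prescriptions, as the instrument, and reports risk differences.

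Under Exposure measures, marginal structural models for treatment switching are set aside partly because "these methods require the strong assumption that there are no unmeasured confounders".

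**The concern.** Triangulation is informative about a bias when the methods would respond to that bias differently. A confounder missing from the Confounding factors list is missing from both the adjusted Cox model and the propensity model, so it pushes both hazard ratios the same way. A reader told that the methods rest on distinct assumptions may take a second, similar hazard ratio as independent support for a causal effect. The article plans recommendations to the FDA and MHRA, so the weight placed on agreement matters.

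There is also a scale problem. Analyses 1 and 2 give hazard ratios and Analysis 3 gives risk differences. The one contrast that bears on unmeasured confounding is therefore the one that cannot be read directly from the planned output.

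**Working it through.** **1. The three analyses side by side** (Confounding factors; Analyses 1 to 3)

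| | Analysis 1 | Analysis 2 | Analysis 3 |
|---|---|---|---|
| Exposure | actual prescription | actual prescription | prescription, instrumented by preference |
| Covariates | measured list | same list | not the basis of identification |
| Entry and exit | first prescription to event or censoring | same | fixed windows, 3 to 48 months |
| Model | Cox, adjusted | Cox, matched sample | additive structural mean model |
| Needs no unmeasured confounding | yes | yes | no; needs a valid instrument |
| Other requirement | correct outcome model | correct propensity model, overlap | instrument assumptions |
| Scale | hazard ratio | hazard ratio | risk difference |

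Analyses 1 and 2 differ in modelling, overlap and target population. They do not differ on unmeasured confounding.

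**2. Illustrative simulation.** All parameters are assumed and none comes from the article: n = 8000 and 30 runs per scenario; three measured covariates; where present, an unmeasured confounder with coefficient +0.7 on the log hazard and −0.7 on the log odds of treatment; a valid instrument. A linear IV estimator stands in for the planned structural mean model.

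| Scenario | Cox HR | Matched HR | Same verdict at 5% |
|---|---|---|---|
| No effect, no unmeasured confounder | 0.97 | 0.96 | 97% |
| No effect, unmeasured confounder | 0.65 | 0.64 | 97% |
| No unmeasured confounder, Cox covariate form wrong | 1.04 | 1.00 | 87% |
| No unmeasured confounder, effect varies with a covariate | 1.09 | 0.98 | 67% |

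In the second row the log hazard ratios correlated at 0.93 across runs, and the IV risk difference averaged −0.006 (SD 0.049). The verdicts matched equally often with and without the unmeasured confounder, so agreement did not discriminate on that point. Agreement did fall under misspecification and heterogeneity, so it carries some information about modelling.

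**3. The article's earlier mortality results** (Power calculations). The adjusted Cox HR at 9 months was 0.49 (0.40 to 0.61), while "instrumental variable analysis found a risk difference of 0.7 (95% CI −3.3 to 4.7) per 1000 patients treated after 9 months".

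- The article's projection reproduces: interval breadth 4.7 − (−3.3) = 8.0; 8.0 / 1.3 = 6.15, stated as 6.2.
- To put the HR on the IV scale, take a comparator risk of p per 1000. The article does not give p, so it is an assumption. Risk difference ≈ −(1 − 0.49)p = −0.51p.
- p = 3 gives −1.5 per 1000, inside the IV interval. p = 10 gives −5.1, outside it.
- The crossing point is p = 3.3 / 0.51 ≈ 6.5 per 1000.
- With the projected breadth of 6.2 and the same point estimate, the interval would be 0.7 ± 3.1, or −2.4 to 3.8. The crossing point would be 2.4 / 0.51 ≈ 4.7 per 1000.

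Without p, the article's figures cannot show whether the two earlier results are compatible. An adjusted risk difference printed beside the IV estimate would allow that comparison.

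**The case against.** The sentence describes three approaches together, and the IV analysis does rest on a different identifying assumption. Analyses 1 and 2 also differ in their modelling, overlap and target-population requirements. Unobserved confounding is admitted in the next item of the list. The remark on marginal structural models concerns treatment switching and time-varying confounders, a more demanding setting than baseline adjustment. Rules for weighing discordant methods could sit in a fuller document. All of this stands. It narrows the point to a printed sentence that is accurate for one contrast and misleading for the other, and to a general disclosure that does not say which methods are exposed.

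A reader might infer more, in three ways that the documents do not support:

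- That agreement of Analyses 1 and 2 is almost guaranteed and uninformative. The 67% and 87% rows above show that the two can diverge and that agreement is some check on modelling.
- That the plan would accept an effect when two of three methods agree. It states no vote or agreement rule, so no error rate can be attached to one.
- That the earlier mortality results conflict and 0.49 is a confounded figure. The IV interval covers benefit and harm, and the comparator risk is not given.

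An endogeneity test from ivreg2 does not compare the IV estimate with a Cox hazard ratio. That objection is met by adding a linear risk difference, which relies on the same no-unmeasured-confounding assumption as Analyses 1 and 2.

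**Conclusion.** The point holds in limited form. Analyses 1 and 2 share the no-unmeasured-confounding assumption and the covariate list, the article does not say so, and its statement about assumptions suggests otherwise. Their agreement checks the handling of measured covariates; evidence on unmeasured confounding comes only from comparing that line with the IV estimate, and only if the instrument is valid.

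The shared assumption follows from the article's own descriptions and needs no simulation. The simulated figures show direction only, and no bias can be quantified for this study from the documents. No planned estimate, model or sample size is wrong on this account. What changes is how much support agreement may be said to give.

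**What to change.** 1. In the strengths and limitations list, replace the sentence on assumptions with one to this effect: Analyses 1 and 2 both assume no unmeasured confounding given the measured covariates; the IV analysis relaxes this at the price of the instrument assumptions.
2. In Statistical analysis and Analysis 3, state that Analyses 1 and 2 count as one line of evidence on unmeasured confounding, with the matched analysis as a check on modelling and overlap.
3. For each binary outcome and window, report the covariate-adjusted linear risk difference beside the IV risk difference, with the ivreg2 endogeneity test, so that the comparison is on one scale.
4. Where the IV interval includes both zero and the adjusted risk difference, report that unmeasured confounding is unresolved, and do not report that the methods agree.

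The cost is a few sentences, one extra linear model per outcome and window, and one option in runs already planned. The endogeneity test will have low power for rare outcomes, so a non-significant result should not be read as absence of confounding. Some findings will be described as resting on one line of evidence instead of two or three methods.

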## Introduction

Smoking is the major cause of preventable morbidity and mortality in the UK and internationally.^1^
^2^ Smoking is also the principal cause of health inequalities and is responsible for most of the difference in healthy life-expectancy between the richest and poorest in our society^3^ and those with and without mental health problems.^4^
^5^ Smoking-related illnesses are estimated to cost the NHS approximately £5billion per year.^6^ Varenicline has been shown to be the most clinically effective smoking cessation medicine for short-term abstinence in randomised controlled trials (RCTs).^7^ However, there is relatively little evidence for its long-term effectiveness and impact on clinical outcomes.

Concerns have been raised that varenicline may be associated with a higher risk of adverse events, including suicide and self-harm and cardiovascular events, than other smoking cessation interventions.^8–11^ In 2009, the US Food and Drug Administration (FDA) mandated that varenicline carry a black box warning (the agency's strongest safety warning) highlighting the increased risk of suicidal ideation and depression in patients prescribed varenicline. This was based on spontaneous reports to the FDA Adverse Events Reporting (FDA AERS) database.^12^ These warnings are meant to indicate causal effects of pharmaceuticals. However, there are an increasing number of experimental and observational studies that suggest there is little difference in risk of adverse neuropsychiatric effects of varenicline compared to nicotine replacement products.^11^
^13^ In October 2014, the FDA decided that the black box warning on varenicline should remain; it is expected that this guidance will be updated after publication of the results of the EAGLES randomised trial in late 2015.^14^
^15^

Much of the evidence about the potential adverse effects of varenicline comes from observational studies, which are prone to confounding. We will add to the evidence base about the possible adverse and beneficial effects of prescribing different smoking cessation medications using three statistical approaches to overcome confounding: multivariable adjusted regression, propensity score regression and instrumental variable analysis. Using these three approaches we aim to examine the effects of varenicline versus other smoking cessation pharmacotherapies on smoking cessation, health service use, all-cause and cause-specific mortality and physical and mental health conditions. Follow-up will end with the earliest of either an ‘event’ or censoring due to the end of registration or death. We will not investigate bupropion because it is rarely prescribed and systematic reviews have found that it is less effective than varenicline for smoking cessation.^7^

### Study aims

What is the effect of varenicline on smoking abstinence? We will investigate the effects of varenicline on smoking abstinence because existing evidence from RCTs typically only followed participants for 1 year, and are not informative about long-term outcomes.What are the effects of varenicline on NHS service use? We will investigate the effects of varenicline prescriptions on all-cause primary and secondary care utilisation because smoking increases morbidity and imposes major costs on the healthcare services.^16^What are the effects of varenicline on all-cause and cause-specific mortality? We will investigate the incidence illnesses in the Clinical Practice Research Database (CPRD) using primary care diagnoses, admission to secondary care using ICD-10 codes, and Office of National Statistics (ONS) mortality records to maximise the number of events detected.What are the effects of varenicline on common physical and mental health conditions? We will investigate the effects of varenicline on rates of cardiovascular outcomes and respiratory illnesses, as previous research has suggested that patients prescribed varenicline may have different rates of these outcomes.^9^
^10^ Second, we will investigate the effects of varenicline on rates of depression and anxiety because there has been some reports that varenicline may reduce the risk of these outcomes.^13^We will also examine differences in smoking cessation medication effectiveness by socioeconomic position. A recent systematic review reported that stop-smoking services may be helping to reduce inequalities in smoking prevalence by preferentially targeting smokers of lower socioeconomic position (SEP). Data from primary care records The Health Improvement Network (THIN) show that between 2008 and 2010, smokers in more deprived groups were more likely to receive smoking cessation interventions.^17^

## Methods and analysis

We will conduct a prospective cohort study of all patients prescribed varenicline or nicotine replacement products in the CPRD. Variables will be defined using ‘Read codes’ which are clinical encoding of patient phenomena, for example a patient's: occupation, demographic information, social circumstances, clinical symptoms and observations, laboratory tests and results, and diagnoses.

### Inclusion and exclusion criteria

We will include patients who were older than 18 and were prescribed medicines in British National Formulary (BNF) category 4.10.2 (Nicotine Dependence) from 1 September 2006, when varenicline was introduced to the UK, to the present. We will use patients prescribed other smoking cessation products (nicotine patches, gum, lozenges, and inhalers) as controls for patients prescribed varenicline. We will include patients whose records were classified as ‘acceptable’ by the CPRD from all ‘up to standard’ general practices (GPs) at least 18 months prior to date of entry of each cohort (1st March 2005). Up to standard GPs are practices that have submitted data that meets the CPRD quality control thresholds. Patient data are defined as ‘acceptable’ by the CPRD if they meet minimum quality control standards, for example their registration period with their GP is valid.

We will exclude patients who registered at a GP less than 365 days before the first recorded prescription, to allow for high-quality assessment of baseline data and possible confounders. Patients prescribed bupropion in the year before their index prescription of varenicline or nicotine replacement therapy will be excluded from the analysis. In the primary analysis we will exclude patients initially prescribed nicotine replacement therapies and varenicline together, although in our previous analysis this only occurred for 0.25% of all prescriptions.^13^

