### Data analysis

#### Exposure measures

First time users of the smoking cessation therapies (varenicline or nicotine replacement therapy) will be defined as people who received at least one prescription of the product after the 1 September 2006 but with no use of a related product during the 12 months before the index date (the first date on which a prescription was issued). Langley *et al*^19^ found the smoking cessation prescription data in the THIN database, which is closely related to the CPRD, to be highly comparable to national dispensing data. The prescriptions will be defined by the therapy file in the CPRD, which contains a list of all prescriptions issued to patients by their GP. Each therapy record records the date a prescription was issued, the quantity of drug prescribed and the dose.

The primary analysis will be limited to the first treatment episode. This is analogous to an intention-to-treat analysis in a RCT.^20^ This ensures that the target parameter estimated in the observational study will be comparable to the parameter estimated by a RCT. For example, if patients’ treatment adherence and duration is related to whether they experience adverse events, then definitions of exposure which are based on treatment adherence may provide unreliable evidence of the causal effect of the prescription on adverse outcomes. This analysis framework was described in Hernán *et al* (2008). The intuition is that most randomised trials recruit individuals and then split participants into different treatment arms. This means that comparison groups are implicitly from first treatment. The primary analysis in an RCT typically reports an intention to treat estimate, which is the difference in allocation between arms of the trial based on allocation, rather than the treatment the participant received. To obtain results that are comparable to a randomised trial Hernán argued that analysts need to construct cohorts that also follow-up patients from first treatment, rather using retrospectively defined exposures (eg, retrospectively defining exposure as ever exposed to varenicline).

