#### Outcome measures

##### Outcome 1: Smoking abstinence

In the CPRD smoking status is indicated by whether the patient is a current, former or never smoker. As GPs are paid to record smoking status smoking behaviour is robustly recorded in the CPRD.^21^ Marston *et al*^21^ found that 84% of patients had smoking status recorded within a year of registering at a GP, and that smoking prevalence rates by age were similar in CPRD and the Health Survey of England. Booth *et al*^22^ found that the difference in prevalence of smoking estimate between the CPRD and the Health Survey for England was less than 1%, and the mean difference was 0.1% (95% CI −1.5% to 1.7%). Using unpublished data from CPRD sampled as part of the research reported in Thomas *et al*^13^ we found that 74% of patients prescribed smoking cessation medication had a subsequent record indicating smoking status. Of these 66% were indicated as current smokers and 33% as ex-smokers. We will initially define a patient as relapsed if they have any record indicating that the patient is a current smoker after their first prescription of a smoking cessation therapy. We will not be able to determine the smoking status of patients who do not return to the GP. Therefore, we will perform sensitivity analyses to examine whether the assumptions made about the smoking status of individuals who are not observed affect the results. For example, we will conduct a sensitivity analysis to see if the results are altered by assuming that patients with missing data have relapsed, or by assuming that patients with missing outcome data have achieved abstinence.

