#### Confounding factors

We will include gender, age in years at time of first prescription, previous psychiatric illness/consultation, previous use of psychotropic medications such as hypnotics, antipsychotics and antidepressants, previous self-harm, measures of alcohol consumption where appropriate mean/median number of GP visits per year, body mass index, SEP (deprivation score for area or residence) and major chronic illness (including: diabetes, cancer, arthritis) using the Charlson index.^26^
^27^ Relevant Read codes will be identified either by validated code lists or by searching for each of these events in the Read code dictionaries to identify any missing Read codes. Collider bias is a potential threat to the analysis; this type of bias occurs when the association between two variables changes on conditioning of a third variable if the third variable is affected by the first two variables. Collider bias could occur if we conditioned on events that happened as a result of the prescription the patient was issued. To prevent this bias from affecting our results, we will define each covariate using data inputted prior to the first prescription.^28^ If there are missing data in the covariates we will consider using multiple imputation.

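### The fixed covariate list has no pre-index smoking variable, and neither the entry criteria nor the abstinence rule considers smoking status at index

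*Protocol article*

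**What the plan says.** Entry. Under Inclusion and exclusion criteria, the core rule is "We will include patients who were older than 18 and were prescribed medicines in British National Formulary (BNF) category 4.10.2 (Nicotine Dependence", followed by conditions on data quality and on bupropion and combined prescriptions, and by a registration rule: "We will exclude patients who registered at a GP less than 365 days before the first recorded prescription". Exposure measures adds a new-user rule: "but with no use of a related product during the 12 months before the index date". These conditions concern records, registration and earlier medication. None concerns whether the patient smokes at index.

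Covariates. Confounding factors gives an explicit list. It opens with "We will include gender, age in years at time of first prescription, previous psychiatric illness/consultation, previous use of psychotropic medications", goes on through self-harm, alcohol, GP visits and body mass index, and closes with "SEP (deprivation score for area or residence) and major chronic illness (including: diabetes, cancer, arthritis) using the Charlson index". All covariates are to be measured before the first prescription. Smoking status, intensity and earlier quit attempts do not appear. Analysis 1 reports "results adjusted for all measured covariates described above". Analysis 2 builds its propensity score from the same list, and the deprivation subgroup analyses refer back to it.

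Outcome. The rule under Outcome 1 is "We will initially define a patient as relapsed if they have any record indicating that the patient is a current smoker after their first prescription". The example sensitivity analyses vary only what is assumed about patients whose later status is missing.

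**The concern.** Outcome 1 asks whether patients stop smoking after a prescription, and status at the start is the most direct prognostic variable for that question. Some patients may already have stopped when the first GP prescription is issued, for example with products obtained elsewhere, and receive nicotine replacement or varenicline to stay off cigarettes. For them the outcome is already reached at time zero. If they remain ex-smokers in the record, their abstinence is credited to the index drug.

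If such patients are more common with one drug than with the other, the comparison of abstinence is confounded, and nothing in the adjustment set of Analyses 1 and 2 corrects for it. The plan can see the variable: it codes patients as current, former or never smokers, relies on that coding for the outcome, and requires a year of registration so that baseline data are good.

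**Working it through.** **Inputs from the Protocol article.** Outcome 1: 74% of patients have a later smoking record; of these, 66% are current smokers and 33% ex-smokers. Power calculations: 110 000 earlier patients plus 18 000 a year for 4 years, given as around 180 000.

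**The plan's own figures.**
- Sample size: 110 000 + 4 × 18 000 = 182 000, which agrees with around 180 000.
- Whole-cohort terms: 0.74 × 0.66 = 48.8% later current smokers; 0.74 × 0.33 = 24.4% later ex-smokers; 26% with no later record.
- Abstinence is therefore 24.4% if missing means relapsed, 33% among those recorded, and 24.4% + 26% = 50.4% if missing means abstinent. None of the three separates patients who were ex-smokers at index.

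**Illustrative model (f and a are assumptions).** Let f be the share already stopped at index, a their chance of never being recorded as a current smoker afterwards, and q abstinence among true index smokers. Then observed abstinence = f·a + (1 − f)·q. The 33% describes all prescribed patients with a later record, so it already contains any index ex-smokers. The overall rate is therefore held at 33%, giving q = (0.33 − f·a)/(1 − f). I take a = 0.8, with a range of 0.6 to 1.0.

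*Share of counted abstainers who had already stopped, f·a/0.33:*
- f = 2%: 0.016/0.33 = 4.8% (3.6 to 6.1%); q = 32.0%
- f = 5%: 0.040/0.33 = 12.1% (9.1 to 15.2%); q = 30.5%
- f = 10%: 0.080/0.33 = 24.2% (18.2 to 30.3%); q = 27.8%

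*Equal f in both arms.* There is no spurious difference. If the drug makes no difference among those already stopped, a true risk difference shrinks by the factor (1 − f): at f = 5%, 5.0 × 0.95 = 4.75 points.

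*Unequal f, no true effect.* The spurious difference is (f₁ − f₂)(a − q), with q taken at the mean f (arms of equal size):
- 2% versus 5%: q = (0.33 − 0.028)/0.965 = 0.313; 0.03 × (0.8 − 0.313) = 1.5 points (0.8 to 2.1)
- 5% versus 10%: q = (0.33 − 0.06)/0.925 = 0.292; 0.05 × (0.8 − 0.292) = 2.5 points (1.5 to 3.6)

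The difference favours whichever arm has more index ex-smokers. The documents do not say which arm that would be.

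*Scale.* With 0.74 × 180 000 = 133 200 recorded patients, 33% abstinent and half on varenicline, the 95% half-width is 1.96 × √(0.33 × 0.67 × 2/66 600) = 0.5 points. With 30% on varenicline it is 0.55. Clustering is ignored and would widen both. At a − q = 0.487, an imbalance in f of about 0.5/0.487 ≈ 1 percentage point would equal that half-width.

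These are risk differences. Analyses 1 and 2 report hazard ratios, so the figures show only the order of magnitude under the stated assumptions.

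**The case against.** The case on the other side is substantial, and much of it limits how far the point goes.

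- A reader might infer that entry rests on a prescription alone. It does not: registration, data-quality, bupropion and new-user rules also apply. The new-user rule removes patients with a recorded GP course in the previous year, and a prescription for nicotine dependence makes current smoking likely. Still, none of these rules checks smoking status, and products obtained outside the GP are not in the therapy file.
- A reader might infer that every index ex-smoker is scored as a success. That is too strong. One later recorded as a current smoker counts as relapsed, and one with no later record falls under the planned missing-data scenarios. Only those recorded afterwards as ex-smokers and never as current smokers are counted as abstinent.
- A reader might infer that all three analyses are biased. The outcome rule is the same in both arms, so bias between drugs needs unequal shares. If prescribing preference is unrelated to patients' status at index, Analysis 3 yields no spurious contrast, although the dilution remains.
- The article acknowledges unobserved confounding and relies on triangulation. That answers variables the plan cannot see, not one that it holds.
- A separate protocol approved by the data provider's committee is mentioned and not shown. Derivation details may sit there. The covariate list, however, is stated in full here and the models are tied to it.

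**Conclusion.** The point holds in limited form. Followed as written, the plan leaves pre-index smoking status out of the Cox, propensity score and deprivation subgroup models, and neither entry nor Outcome 1 takes account of it. The consequence is confounding of the abstinence contrast in Analyses 1 and 2 if the share already stopped differs by drug. If the share is equal, the consequence is slight dilution and overstated absolute abstinence.

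The size is unknown, because the documents give neither the share nor its direction. The earlier results under Power calculations (the self-harm hazard ratio moving from 0.73 to 0.90, and the mortality ratio from 0.43 to 0.49, on adjustment) show that the two groups differ on measured characteristics. They do not show that status at index differs. The calculated differences are conditional on assumed values of f and a, and are not evidence of a bias of that size or of a bias against either drug.

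A reader might also conclude that the main analysis should be restricted to recorded current smokers. The documents do not support that. The last record may be out of date, and a former smoker who relapsed and then sought treatment would be wrongly dropped. The article's evidence on recording concerns completeness after registration and population prevalence, not whether status is current at index.

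**What to change.** Derive the latest smoking-status record on or before the index date, with cigarettes per day where recorded. Add it to the Confounding factors list, so that it enters the Cox models, the propensity score and the deprivation subgroup analyses, and report its distribution by arm. That table would also show how large the issue is.

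Keep the full prescribed cohort as the main analysis of Outcome 1, and add a sensitivity analysis restricted to patients whose latest pre-index record is current smoker. The other outcomes keep the full cohort.

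The cost is a short change of wording, a small number of derived variables from data the plan already uses, and one further sensitivity analysis. The variable satisfies the plan's rule that covariates precede the first prescription, and missing values can follow the multiple imputation already under consideration. The sensitivity analysis loses some genuine smokers with an outdated or absent record, which is why it should not replace the main analysis.
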